### 2.8. Safety outcomes

Safety outcomes will be any adverse events that occur during the 4-week treatment, such as localized tingling, redness, swelling, or other adverse reactions due to electrical stimulation.

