**Methods::**

This is an 8-week, randomized, controlled pilot trial with 3 parallel groups. In a ratio of 1:1:1, 120 patients with stage 1 hypertension will be divided into the TEAS-2Hz group, TEAS-10Hz group, or usual care group. All patients will receive the usual care for hypertension including lifestyle education, etc. Additionally, the 2 TEAS groups will receive 12 sessions of TEAS interventions at 2 Hz or 10 Hz, 3 times weekly for 30 minutes each, with 4 weeks of follow-up. The main outcome will be the change from baseline to week 4 in systolic BP among the groups. Secondary outcomes consist of changes in diastolic BP, mean arterial pressure, heart rate, heart rate variability, medication adherence, and quality of life. The safety outcomes will be any adverse event during the treatment.

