#### 2.5.2. TEAS groups.

To exploratively observe the hypotensive effect of different stimulation frequencies, this trial will set up 2 TEAS groups, in which patients will respectively receive TEAS at 2 Hz or 10 Hz, with the addition of their routine care. The interventions will last for 12 sessions of 30 minutes each, 3 sessions per week for 4 weeks. The treatment will be conducted using the TENS mode of a low frequency pulse electroacupuncture instrument (XS-998B06, Nanjing Xiaosong Medical Instrument Research Institute, Nanjing, China).

Every instrument has 6 output channels, each connected to a pair of square electrodes (40 mm × 40 mm). The patient is expected to fully expose the acupoints of the limbs in a comfortable sitting position. After cleaning the skin, bilateral acupoints will be applied by electrodes. Each pair of electrodes is connected to 3 groups of acupoints on the same side of the limb, and the acupoints are Quchi (LI11) and Hegu (LI4), Neiguan (P6) and Ximen (PC4), Zusanli (ST36) and Taichong (LR3). Figure 2 shows the location of the acupoints and the connection method with the instrument. The instrument outputs a bidirectional symmetrical narrow square wave with a pulse width of 0.4 ms-0.6 ms. The output frequency will be set at 2 Hz or 10Hz depending on the grouping of patients. The stimulation intensity of each output is adjusted to the maximum intensity tolerated by the participant and causes no pain or discomfort, and the stimulation will last for 30 minutes.

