### 2.7. Secondary outcomes

Secondary outcomes will involve the change in DBP, mean arterial pressure, heart rate (HR), heart rate variability (HRV), 8-item Morisky medication adherence scale (MMAS-8), and 12-item health survey (SF-12) among the 3 groups at different time points.

The measurement of DBP and HR will be the same as SBP, at baseline, every week, and follow-up. Mean arterial pressure indicates the function of the heart and the resistance of the peripheral aorta, and it can be calculated according to this formula:^[30]^

MAP ​​ ​​ =DBP ​​ ​​ + ​​ ​​ 1/3 ​​ ​​ (SBP ​​ ​​  ​​ ​​ DBP).

Analysis of HRV can reflect the activity, homeostasis, and associated pathology of the cardiac autonomic nervous system.^[31]^ In this trial, HRV will be measured by a flexible dynamic ECG monitor (CH-E31, Zhejiang Zhi Yu Technology Co., Ltd., Zhejiang, China) at baseline, week 1, and week 4. This instrument should be attached to the left chest, about 1 finger from the clavicle, as shown in Figure 2. Before the assessment, the patient will be asked to be relaxed and quiet for at least 10 minutes and will not be verbally informed of the measurement start point, which may affect the results.

The data will be analyzed in the frequency domain from a 5-minute recording, involving low frequency (LF), high frequency (HF), LF/HF ratio, total power, very low frequency, normalized low frequency (LF norm) and normalized high frequency (HF norm).

The MMAS-8, consisting of 8 brief questions, is the most commonly used scale to investigate medication adherence in people with hypertension.^[32]^ The SF-12 is valid and equivalent for Chinese people and consists of physical component summary and mental component summary.^[33]^ Patients are advised to fill out both questionnaires at baseline, week 4, and at follow-up. Supplemental Digital Content 1, http://links.lww.com/MD/J83 shows the above 2 questionnaires.

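### The safety outcome closes at week 4 of an 8-week trial, so adverse events that begin during follow-up do not count in any of the three groups

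*Protocol article*

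**What the plan says.** Section 2.8 defines the safety outcome with an explicit end: "Safety outcomes will be any adverse events that occur during the 4-week treatment". It then lists examples, all of them local or stimulation-related reactions. The Abstract (Methods) repeats the limit: "The safety outcomes will be any adverse event during the treatment".

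The trial itself runs longer. The Abstract opens its Methods with "This is an 8-week, randomized, controlled pilot trial with 3 parallel groups" and describes the TEAS schedule as "3 times weekly for 30 minutes each, with 4 weeks of follow-up". Section 2.5.2 fixes the treatment period: "The interventions will last for 12 sessions of 30 minutes each, 3 sessions per week for 4 weeks".

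Assessment continues after treatment ends. Section 2.7 measures diastolic pressure and heart rate, in the same way as systolic pressure, "at baseline, every week, and follow-up". For the adherence and quality-of-life scales it says: "Patients are advised to fill out both questionnaires at baseline, week 4, and at follow-up". Section 2.5 has medication use recorded for the whole trial. The Introduction names the safety of TEAS, compared with usual care, as one of the aims.

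**The concern.** The plan observes patients for efficacy and quality of life after treatment stops, but its safety outcome ends with treatment, and it gives no reason for the difference. Two kinds of event would fall outside the outcome if the definition is followed: reactions with late onset, and events that begin after TEAS is withdrawn from patients whose blood pressure it may have lowered.

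This is a rule stated in two places, so it is not a detail that a condensed article has left to a fuller document. The Abstract's Discussion presents the trial as preparation for a larger one, and that trial would take its safety expectations from this result. A safety table that stops at week 4 can say nothing about the month after stopping, although the patients will have been seen again.

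**Working it through.** **Inputs**

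| Item | Value | Source |
|---|---|---|
| TEAS sessions | 12, at 3 per week | Section 2.5.2 |
| Follow-up after treatment | 4 weeks | Abstract, Methods |
| Stated trial length | 8 weeks | Abstract, Methods |
| Safety window | the 4 treatment weeks | Section 2.8; Abstract, Methods |
| Assessments after treatment | blood pressure, heart rate, both questionnaires | Section 2.7 |
| Patients | 40 per group, 120 in total, 80 on TEAS | Sections 2.1 and 2.9 |

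**Step 1: reproduce the stated trial length.** 12 sessions / 3 per week = 4 weeks of treatment. 4 + 4 weeks of follow-up = 8 weeks, which matches the Abstract. The end of follow-up is therefore week 8. Section 2.7 does not itself date the follow-up assessment.

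**Step 2: the share of planned observation inside the window.** 4 / 8 = 50% of calendar time. With all 120 patients and no dropout, 120 x 4 = 480 of 120 x 8 = 960 patient-weeks lie outside it. Of those 480, 40 x 4 = 160 belong to usual care and 80 x 4 = 320 to the two TEAS groups.

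**Step 3: set the definitions side by side.** Section 2.8 and the Abstract agree that the safety outcome ends with treatment. Section 2.7 shows that contact with patients does not. No readable part of the document brings events from weeks 5 to 8 into the safety outcome.

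**Step 4: what could be missed (illustration only).** The documents give no risk for an event starting in weeks 5 to 8, so a range is assumed. For a per-patient risk p, the chance of at least one such event among the 80 TEAS patients is 1 - (1 - p)^80, and the expected number of patients affected is 80p.

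| Assumed p | Expected patients affected | Chance of at least one |
|---|---|---|
| 1% | 0.8 | 55% |
| 2% | 1.6 | 80% |
| 5% | 4.0 | 98% |

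Under the stated definition none of these would count. The table shows only that small late risks would be visible in a trial of this size if they were counted. It is not evidence that such risks exist.

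**The case against.** The strongest reply is that an on-treatment window is a coherent choice. The Abstract and Section 2.8 agree with each other, and the window ends when the primary outcome is measured, at week 4. TEAS is a surface treatment given in 30-minute sessions, and the reactions named would be expected at or soon after a session. A rise in pressure after stopping would show in the follow-up blood pressure readings. The schedule (Table 1) is not readable and may show adverse events being recorded at follow-up.

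Much of this stands. There is no internal contradiction, and the document does not say that later events go unrecorded. What remains is that the defined outcome would not count them, and that a blood pressure reading at follow-up does not capture a clinical event between visits.

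A reader might also infer more than the text supports:

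- **That half of the safety information is lost.** The 50% is calendar time. Equating it with information assumes the same risk in weeks 5 to 8 as in weeks 1 to 4, which is unlikely for local reactions, and a third of the excluded patient-weeks (160 / 480) are in usual care.
- **That the short window makes the groups unequal.** It is the same period in all three groups, so the problem is incomplete capture and not uneven ascertainment.
- **That unattributed events are excluded.** The definition covers any adverse event, and the stimulation-related reactions are introduced as examples. Tighter wording would help, but nothing rules out unrelated events or events in usual care.
- **That the precision of a zero count depends on the window.** With 0 events in 80 patients, the one-sided 95% upper limit is 1 - 0.05^(1/80) = 3.7%. This depends only on the 80 patients. A longer window changes the period to which the limit refers, not its value.

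**Conclusion.** The point holds as a cheap improvement to a stated rule. The safety outcome covers 4 of the 8 planned weeks, and events that begin in weeks 5 to 8 fall outside it in all three groups, although patients are assessed again and safety against usual care is an aim. The practical weight is modest: the reactions named would mostly appear during treatment, and the size of any late risk cannot be derived from the documents.

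The conclusion rests on reading Section 2.8 and the Abstract literally, and on taking the end of follow-up as week 8 from the Abstract. It does not assume that later events go unrecorded. If Table 1 shows that they are collected, the remaining step is to include them in the outcome.

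**What to change.** Redefine the safety outcome in Section 2.8, and match it in the Abstract, as all adverse events, whatever the suspected cause, from randomisation to the end of follow-up in all three groups. Starting at randomisation gives usual care, which has no first session, the same starting point. Ask about events in the same way in every group at the weekly and follow-up blood pressure assessments. Report weeks 1-4 and weeks 5-8 separately, so that the on-treatment result stays visible. If the sponsor prefers to keep the week-4 limit, the protocol should give the reason.

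The cost is a change of wording, one added question at contacts already planned, and a slightly longer safety table. Neither the sample size nor the visit schedule changes.

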### 2.9. Sample size calculation

This pilot trial focuses on the effects of TEAS for hypertension and the optimal stimulation frequency, so as to be a preliminary for the further clinical trial. In accordance with Provisions for Drug Registration in China, the minimum number of cases (experimental group) for exploratory clinical trials is required to be 20 to 30. Browne^[34]^ considers that a sample of 30 cases is not sufficient to ensure confidentiality unless the effect size is very large. Kieser et al^[35]^ and Hertzog^[36]^ recommended 20 to 40 cases as an empirical estimate of the sample size for pretesting. Accordingly, taking full consideration of the above recommendations and the shedding rate, 40 participants per group and a total of 120 participants in 3 groups were determined.

### 2.10. Statistical analysis

The statistical software IBM SPSS Statistics (25.0, NY) will be selected for data analysis. Statistical analysis will be conducted following the principle of intention-to-treat (ITT), which involves all patients randomly assigned in the trial for ensuring the randomization principle. Missing data will be processed by the method of multiple imputation. Continuous data will be indicated as mean ± standard deviation or median and interquartile range, based on whether the normality is satisfied. As for measurements at different time points, repeated measures ANOVA and Bonferroni post hoc tests will be used for evaluation. Categorical data will be described as frequencies and percentages, and the difference among groups will be analyzed by the chi-square test or Fisher exact test. In a 2-sided test at *P* < .05, the difference will be deemed statistically significant.

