## 2. Methods

### 2.1. Study design

This study is a randomized, controlled pilot trial with 3 parallel groups. A total of 120 hypertensive patients meeting the inclusion criteria will be recruited and then randomly allocated to 3 groups of 40 patients each. All 3 groups will receive 4 weeks of usual care, and TEAS intervention groups will be additionally treated with TEAS treatment (2 Hz or 10 Hz). We will keep the stimulation location, duration, waveform, and other parameters the same for comparing the effects of different frequencies of TEAS in hypertension. The study protocol has obtained approval from the ethics committee of Beijing University of Chinese Medicine (No. 2022BZYLL1207), as well as registration at the Chinese clinical trial registry (ChiCTR2200067147). The protocol will be reported in compliance with the Standard Protocol Items (SPIRIT). The outline of the study protocol is displayed in a flow chart (Fig. 1), while the schedule of the trial process is illustrated in Table 1.

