### 2.6. Primary outcome

The primary outcome will be the change in office SBP among the 3 groups from baseline to the end of the intervention (week 4). The measurement of BP will be performed with an electronic sphygmomanometer (KC2110, Shaanxi Kangshengshi Electronic Technology Co., Ltd., Shaanxi, China). Patients will be required to sit in silence for at least 5 minutes before taking their BP. Keeping the upper arm at the level of the heart, both arms will be measured at baseline and the side with the higher BP will be chosen for subsequent testing. To ensure the accuracy of the recording, the independent outcome assessor will repeat the BP measurement 3 times every 5 minutes and take the mean of the last 2 readings.

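### Section 2.10 does not tie its repeated measures ANOVA to the primary outcome, the week-4 change in SBP, and uses no baseline covariate

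*Protocol article*

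**What the plan says.** Section 2.6 of the protocol article fixes the endpoint: "The primary outcome will be the change in office SBP among the 3 groups from baseline to the end of the intervention (week 4"). Section 2.7 gives the BP schedule: "The measurement of DBP and HR will be the same as SBP, at baseline, every week, and follow-up". The abstract describes the treatment period as followed by a further period, "with 4 weeks of follow-up".

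For continuous data measured over time, the only inferential statement in section 2.10 is: "As for measurements at different time points, repeated measures ANOVA and Bonferroni post hoc tests will be used for evaluation". The criterion is "In a 2-sided test at *P* < .05, the difference will be deemed statistically significant", and missing values are covered by "Missing data will be processed by the method of multiple imputation". Section 2.10 names no model effect, set of visits, week-4 contrast, family of comparisons or covariate.

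**The concern.** A repeated measures ANOVA of three groups over several visits yields three tests: group, time and group-by-time. If every BP visit is entered:

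- The group effect, with post hoc comparisons of group means, averages over all visits. These include baseline, where randomisation leaves no treatment difference, and the follow-up after treatment has stopped.
- The group-by-time test asks whether the profiles differ anywhere over the schedule, not whether they differ in the change to week 4.
- The time effect is not a randomised comparison at all.

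With P < .05 as the only criterion, significance could be declared on an effect that is not the endpoint. Baseline SBP, which is measured on everyone, enters as one more outcome level and is not used to gain precision. The pilot is meant to inform a larger trial and to help choose between 2 Hz and 10 Hz, so a clear week-4 estimate is one of its main products.

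**Working it through.** **Inputs from the article.** Patients are "randomly allocated to 3 groups of 40 patients each" (section 2.1), and 3 × 40 = 120 agrees with the stated total. The two-sided level is 0.05 (section 2.10). There is no power figure to reproduce: section 2.9 sets the size from rules of thumb, "taking full consideration of the above recommendations and the shedding rate", and gives no effect, SD, correlation or dropout rate.

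**Assumptions.** Six BP visits (baseline, weeks 1 to 4 and one follow-up; Table 1 is not shown). Bonferroni over the three group pairs, so 0.05/3 = 0.0167 per pair, z = 2.394. All 40 per arm analysed. SBP SD σ = 10 mm Hg. Correlation between any two visits ρ = 0.5 (range 0.3 to 0.7). True week-4 difference of 5 mm Hg for each TEAS arm against usual care.

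**1. Which test is which.** With six visits, group-by-time has (3 − 1)(6 − 1) = 10 degrees of freedom, and week 4 is one of five post-baseline visits. With only baseline and week 4 it has 2, and it is algebraically the one-way ANOVA of the change score. Simulation of 5,000 trials per scenario gave the two identical rejection rates throughout (for example 62% and 62% at ρ = 0.5).

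**2. Value of baseline adjustment.** The variance per patient is 2(1 − ρ)σ² for the change score and (1 − ρ²)σ² for ANCOVA. The ratio is (1 − ρ²)/[2(1 − ρ)] = (1 + ρ)/2, which gives 0.65, 0.75 and 0.85 at ρ = 0.3, 0.5 and 0.7. This needs no effect size or SD. At ρ = 0.5, 40 per arm with adjustment carries the information of 40/0.75 ≈ 53 per arm without it.

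**3. Effect averaged over six visits.** Let the effect rise linearly: 0, 1.25, 2.5, 3.75, 5 mm Hg from baseline to week 4. With follow-up at 0, 2.5 or 5, the six-visit mean is 12.5/6 = 2.08, 15/6 = 2.50 or 17.5/6 = 2.92 mm Hg.

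**4. Pairwise power at 0.0167.** Power = Φ(difference/SE − 2.394), with SE = SD × √(2/40). At ρ = 0.5:

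| Comparison | SD multiplier | SE | Power |
|---|---|---|---|
| Six-visit mean | √((1 + 5ρ)/6) = 0.764 | 1.71 | 12%, 18%, 25% |
| Week-4 change | √(2(1 − ρ)) = 1.000 | 2.24 | 44% |
| Week-4 ANCOVA | √(1 − ρ²) = 0.866 | 1.94 | 57.5% |

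At ρ = 0.3 the six-visit mean has 17%, 25% and 35% against 48% for ANCOVA. At ρ = 0.7 it has 9%, 14% and 19% against 77%.

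A second set of assumptions (effect 7, SD 12, ρ = 0.5, half the effect kept at follow-up) gives a six-visit mean of 3.5 with SE 2.05, hence 25%. The week-4 change has SE 2.68 (58.5%) and ANCOVA SE 2.32 (73%).

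**5. Omnibus three-arm tests at 0.05.** Simulated power with effect 5, SD 10, equal correlation between visits and Greenhouse-Geisser correction. FU is follow-up.

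| Time course | ρ | Group | Group × time, six visits | Week-4 change | Week-4 ANCOVA |
|---|---|---|---|---|---|
| Rising, gone at FU | 0.5 | 22% | 59% | 62% | 75% |
| Rising, half kept | 0.5 | 31% | 44% | 62% | 75% |
| Rising, fully kept | 0.5 | 40% | 58% | 63% | 75% |
| Full from week 1, gone at FU | 0.5 | 50% | 83% | 62% | 75% |
| Full from week 1, kept | 0.3 | 84% | 41% | 47% | 65% |

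In the last two rows one of the repeated measures tests beats ANCOVA. With no true effect, every test rejected in 4.1% to 5.8% of trials, over equal and decaying correlation structures.

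**The case against.** A reader might infer that the stated method does not test the primary outcome at all. The document does not support that. Section 2.10 leaves the visits and the post hoc comparisons open, so a baseline and week-4 model, or Bonferroni comparisons made at week 4, fits its wording as well as an all-visit model does. Under the two-visit reading the correct quantity is tested and nothing is diluted.

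A reader might also infer that a real week-4 effect is bound to be diluted and power lost. That holds for an effect that builds up to week 4. It can reverse for an immediate effect, and the article gives no time course.

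It could further be thought that multiple imputation rules out ANOVA F tests. It does not, since multi-parameter tests can be pooled across imputed data sets. A single contrast is only simpler to pool.

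Finally, this is a pilot with no power target to miss, an unadjusted change score is unbiased under randomisation, and a separate analysis plan may supply the detail. These points lower the severity. What stands is that the article itself states both the endpoint and the method, and does not connect them.

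**Conclusion.** The point holds as a matter of target and precision. The article leaves open which test decides the primary question, and the all-visit reading would answer a different one. Under every reading the precision from baseline SBP goes unused. On the two-visit reading that is the whole loss: simulated omnibus power of 62% against 75% at ρ = 0.5.

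The power contrasts for the all-visit reading, about 12–25% for time-averaged pairs against 57–73% for week-4 ANCOVA at ρ = 0.5, are illustrative. They rest on an assumed effect, SD, correlation, rising time course and six visits. The size of each single test is not affected. This should be fixed because the improvement is free. It does not invalidate the trial.

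**What to change.** State one primary analysis in section 2.10: week-4 office SBP compared between groups with adjustment for baseline SBP. Use ANCOVA on the multiply imputed data sets or, as an alternative chosen in advance, a mixed model of SBP at weeks 1 to 4 with group, visit, group-by-visit, baseline SBP and baseline-by-visit, read at week 4. Report the three pairwise differences with 95% confidence intervals, and say that Bonferroni covers those three pairs (0.0167 each). With baseline in the model, the adjusted week-4 difference is also the adjusted difference in change, so the endpoint in section 2.6 stays as it is. Keep the weekly profile and follow-up as secondary results.

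The cost is a few sentences in the protocol or analysis plan. No extra patients, visits or data are needed, and standard software fits either model.

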Acupuncture, a vital component of traditional Chinese medicine, has been utilized as a nondrug therapy for treating patients with cardiovascular disease.^[13–15]^ Although the conclusions are varied, most studies suggest that acupuncture is effective in lowering BP as an adjunctive therapy.^[3,16–18]^ Transcutaneous electrical acupoint stimulation (TEAS), as the electrical stimulation portion of biofeedback physical regulation based on acupoints, is a novel acupuncture technique that is noninvasive, integrating the functions of modern transcutaneous electrical nerve stimulation (TENS) and conventional acupoint stimulations.^[19]^ By applying electro-stimulation pulses on aimed acupoints, TEAS delivers similar effects to electroacupuncture, but without the risks of invasive infection, patients psychological fears, or manipulator bias.^[20]^ Meanwhile, Along with the stimulation sites, the stimulation parameters are another crucial factor in the efficacy of TEAS. Evidence for a potential hypotensive effect of TEAS has been provided by some studies, but the optimal stimulation parameters remain unclear.^[21–23]^ The stimulation parameters of TEAS mainly consist of intensity, waveform, and frequency, among which the frequencies used vary widely in different studies, ranging from low frequency to high frequency.^[24,25]^ Studies find that both high frequency and low frequency electrical stimulation have shown some vasodilatory effects.^[26,27]^ but for decreasing BP, low frequency seems to perform better, which may also correlate with its modulation of autonomic nerves.^[21,28,29]^ Also, the low frequency of electrical stimulation is a wide range that requires to be selected optimally.

Based on the above, the pilot trial is expected to investigate the effectiveness and safety of TEAS for hypertension by comparing it with usual care; to explore the optimal transcutaneous electrical stimulation frequency by comparing different stimulation frequencies at 2 Hz and 10 Hz. Further, it will lay a foundation for future large clinical trials and provide a reference for the parameter setting of biofeedback electric stimulation devices.

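### If the Bonferroni family in section 2.10 is the three pairs of arms at week 4, a step-down or closed procedure keeps the same 5% family-wise error with more power per pair

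*Protocol article*

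**What the plan says.** The Introduction gives two aims. The first is to "investigate the effectiveness and safety of TEAS for hypertension by comparing it with usual care". The second is "to explore the optimal transcutaneous electrical stimulation frequency by comparing different stimulation frequencies at 2 Hz and 10 Hz". Section 2.6 defines the primary outcome across all arms: "The primary outcome will be the change in office SBP among the 3 groups from baseline", measured to week 4. The Abstract gives equal allocation of 120 patients, and section 2.9 gives 40 per arm.

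The only multiplicity rule is in section 2.10, in a sentence about measurements taken at different times: "repeated measures ANOVA and Bonferroni post hoc tests will be used for evaluation". The significance level follows: "In a 2-sided test at *P* < .05, the difference will be deemed statistically significant". The section does not say whether Bonferroni runs over pairs of arms, over time points or over both. It defines no contrast that combines the two TEAS arms.

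**The concern.** The natural family for a primary outcome compared among three arms is the three pairs: 2 Hz against usual care, 10 Hz against usual care, and 2 Hz against 10 Hz. Bonferroni would then test each pair at 0.05/3 = 0.0167.

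Three arms are a special case. If any two of the three pairwise equalities are true, the third is true as well. The null hypotheses can therefore hold in only three ways: all three true, exactly one true, or none true. A procedure that protects the all-equal case at 5%, and each single pair at 5%, protects the whole family. Bonferroni still charges for three simultaneous true nulls after that possibility has been ruled out.

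What is at stake is power for each of the named comparisons, in a trial whose size comes from rules of thumb (section 2.9). Validity is not at stake.

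**Working it through.** **Inputs from the protocol article.** Two-sided 5% (2.10); 40 per arm (2.9), and 3 × 40 = 120, which agrees with the stated total; equal allocation (Abstract). Section 2.9 gives no SD, effect or power, so there is no power figure to reproduce.

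**Assumptions.** A standardised effect d (mean difference/SD) from 0.3 to 0.7, one time point (week 4), no dropout, common variance with 3 × 39 = 117 degrees of freedom. Results marked *simulated* come from repeated three-arm trials under these assumptions, 200,000 per scenario in the main runs.

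**Procedures compared**
- Bonferroni: each pair at 0.0167.
- Step-down: smallest p at 0.0167; if rejected, the other two at 0.05.
- Closed: global three-group F test at 0.05; if rejected, each pair at 0.05.

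**Error control (simulated)**

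| True state | Unadjusted pairs | Bonferroni | Step-down | Closed |
|---|---|---|---|---|
| All arms equal: any false finding | 0.121 | 0.043 | 0.043 | 0.049 |
| Both TEAS arms equal and far from usual care: false 2 Hz vs 10 Hz finding | 0.050 | 0.017 | 0.050 | 0.050 |

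Both alternatives stay at or below 5%, up to simulation error. The second row shows the error rate that Bonferroni leaves unused.

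**Power for one TEAS arm against usual care, both TEAS arms equally effective (simulated)**

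| d | Bonferroni | Closed |
|---|---|---|
| 0.3 | 14% | 19% |
| 0.5 | 43% | 53% |
| 0.7 | 76% | 85% |

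Hand check of the Bonferroni column at d = 0.5: the standard error in SD units is √(2/40) = 0.2236, so d/SE = 2.236. Power ≈ Φ(2.236 − 2.394) = Φ(−0.158) = 0.44. At the full 5% level without the global gate it would be Φ(2.236 − 1.960) = Φ(0.276) = 0.61. The closed test lies between the two because of the gate.

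**Step-down rule, one scenario in mm Hg.** Assume SD 12, baseline correlation 0.5 with baseline adjustment, and both TEAS arms 7 mm Hg lower. The residual SD is 12 × √(1 − 0.25) = 10.4, so d = 7/10.4 = 0.67. Power per pair is 0.72 with Bonferroni, 0.79 with step-down and 0.81 with the closed test. Without the baseline adjustment, d = 7/12 = 0.58, and Bonferroni gives 0.58 and the closed test 0.68.

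**At least one significant pair.** Step-down starts with the same test as Bonferroni, so this probability is identical. For the closed test it moves from 0.59 to 0.62 at d = 0.5, and from 0.856 to 0.878 at d = 0.67.

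**Mean of both TEAS arms against usual care (80 vs 40).** SE = √(1/80 + 1/40) = 0.1936.
- Both frequencies at d = 0.5: 0.5/0.1936 = 2.582, and Φ(2.582 − 1.960) = 0.73.
- Only one frequency at d = 0.5: the averaged effect is 0.25, 0.25/0.1936 = 1.291, and Φ(1.291 − 1.960) = 0.25. Bonferroni has 0.44 for at least one TEAS arm against usual care in that case.
- Run as an extra ungated 5% test beside the closed pairs, it raises family-wise error with all arms equal to 7.5%.

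**The case against.** **Bonferroni is valid and conventional, and this is a pilot.** That stands. The type I error is protected, the trial claims no power, and no stated target is missed. A reader might infer that the plan contains a statistical error here. It does not. The case for change is that another rule gives more for the same error limit and costs one sentence.

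**The family is not stated.** That also stands. A reader might take section 2.10 to fix three pairwise tests at 0.0167, but the sentence is about measurements at different time points and gives no such level. The three-arm argument covers one outcome at one time point. It does not carry over to a family that also spans weekly and follow-up visits. The full definition of the family may be in an analysis plan that is not shown, so its absence here is not itself a finding.

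**The first aim is not neglected.** A reader might infer that the plan overlooks a pooled comparison of TEAS with usual care. The Introduction speaks of comparing TEAS with usual care and does not say that the arms are combined. The two pairs against usual care address that aim. Pooling also averages over the frequency difference that the trial sets out to study.

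**The alternatives have a price.** Bonferroni comes with simple simultaneous confidence intervals that match its tests, and the alternatives do not. When both frequencies work equally, a false preference between them occurs 5% of the time where Bonferroni gives 1.7%. That is the nominal rate, but it bears on the choice of frequency, and the sponsor may prefer the stricter level for that pair.

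**Conclusion.** The point holds as an efficiency improvement, conditional on the Bonferroni family being the three pairs of arms for the week-4 change in systolic pressure. Under that reading Bonferroni is stricter than 5% family-wise control requires. Under equal TEAS effects the closed test adds about 5 points of power per pair at d = 0.3, 10 at d = 0.5 and 9 at d = 0.7. The step-down rule adds 7 points at d = 0.67 (0.72 to 0.79) and never rejects less than Bonferroni.

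The gain lies in the individual comparisons. The chance of finding at least one difference rises by 2 or 3 points with the closed test in the cases shown, and not at all with step-down. All these figures rest on assumed effects, since the documents supply none.

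The combined TEAS contrast is useful as an estimate if both frequencies work to a similar degree, and it is clearly worse if only one does (0.25 against 0.44 at d = 0.5). The figures do not support making it the main test.

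**What to change.** In section 2.10, for the week-4 change in systolic pressure, name the three pairs of arms as the family and replace Bonferroni with one of these:
- **Step-down:** test the smallest of the three pairwise p values at .0167; if it is rejected, test the other two at .05.
- **Closed test:** test the three-group hypothesis at two-sided 5%; if it is rejected, test each pair at 5%.

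The step-down rule is the easier choice, because it needs only the three pairwise p values and so fits directly with the multiple imputation already planned.

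The mean of the two TEAS arms minus usual care may be reported with a 95% confidence interval, labelled as a supplementary estimate and without a further ungated significance test.

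Cost: one or two sentences, with no extra patients or data. Pairwise intervals should be labelled as either unadjusted or Bonferroni-adjusted, because neither will always agree with the new test decisions. The 5% false-positive rate for 2 Hz against 10 Hz should be accepted knowingly. Comparisons at other time points need their own rule, which this change does not supply.
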